#### Control hospitals

At baseline, district hospitals in the control group will have similar characteristics to those of hospitals in the intervention group in terms of surgical productivity, PIPES scores and staffing levels (as determined by the findings of the situation analysis). In control sites, practice will continue as standard during the study, without supervision from the SURG-Africa SOTs. The two groups will be followed prospectively and compared to observe any changes as a result of the intervention.

### Study objectives

Our study aims to collect empirical data on a range of output (and in some cases outcome) measures to provide as comprehensive a picture as possible of district-level surgical care, to establish the benefits of the SURG-Africa intervention and to inform national policies and strategies. The evaluation of complex projects such as SURG-Africa requires a variety of tools and multi-level analyses. In order to provide a systematic overview of our evaluation, we have divided our analysis into three broad inter-related feasibility objectives as described below.

#### Objective 1: Surgical preparedness, capacity and productivity

The first objective of our study is to undertake a quantitative assessment of surgical service delivery at district hospitals and how this is affected by the intervention, considering three dimensions: hospital preparedness, capacity and productivity. Each dimension will be measured using quantitative indicators reflecting our overall research aims and conceptual framework, as described in the previous sections. Table 2 provides an overview of objective 1 including indicators, data sources, instruments and planned analyses.

**Table 2 Tab2:** Overview of objective 1

	Indicators	Data collection instruments	Measurement
Preparedness - change in surgical capacity of DLH facilities	Change in Personnel Infrastructure Procedures Equipment Supplies (PIPES) index scores	PIPES questionnaire	Measured at baseline with periodic follow-ups (month 0, month 12, month 24 of the intervention)
Capacity - change in skills of DLH staff	Number of intervention DLH staff who are reported as competent in doing index procedures Intervention DLH staff self-reported surgical skills confidence levels	PIPES questionnaire Self-reported surgical confidence tool	Before-and-after controlled comparison
Productivity - increase in surgical outputs and outcomes	Change in number of index surgical procedures performed by DLHs Types and numbers of new procedures introduced into DLHs Change in surgical mortality rates	PIPES questionnaire Monthly data collection from DLHs operating theatre registers	Comparing differences: (1) before and after and (2) between intervention and control hospitals

It is expected that the intervention will change the *surgical productivity* of DLHs in terms of number of common surgical procedures performed and types and numbers of new procedures introduced, which form the primary endpoint of the study. Monthly numbers of Caesarean sections are typically used to assess the volume of major surgery at DLHs. SURG-Africa will monitor this parameter and include a larger set of core general surgical procedures done in DLHs, identified through the initial situation analysis. This will allow us to develop an index of key procedures to compare differences in numbers and types of procedures: (1) before and after and (2) between intervention and control hospitals, at both group and individual hospital level of analysis. In parallel, the evaluation will track intra-hospital mortality rates to monitor possible changes in surgical outcomes as surgical activity is expected to increase.

Our study will also analyse whether the intervention will result in changes in the key drivers of DLH productivity, namely the *capacity* of local surgical teams and overall *preparedness* of the facilities to perform surgery. The change in staff capacity will be measured through a before-and-after controlled comparison of the number of intervention DLH staff who is reported as competent in doing index procedures. Another measure is self-reported surgical confidence as a proxy parameter for surgical skills. This tool has been tested and validated by previous studies, showing positive correlation between confidence of surgical providers and assessment of skills by their supervisors [57].

At facility level, the change in the surgical capacity of sample DLHs will be assessed through the Personnel, Infrastructure, Procedures, Equipment and Supply (PIPES) index [51]. Since the intervention focuses primarily on strengthening the human capital of DLHs rather than their physical resources (which will also be monitored), it is expected that the only change directly attributable to the intervention will be on the procedures component of the PIPES index (i.e. the range of procedures done in the intervention hospitals). However, while the intervention does not explicitly target the elements of the PIPES tool that do not relate to human capacity, the attention brought by the project through identifying and reporting obstacles to surgical service provision in the districts might indirectly affect the surgical system, at the district and higher levels, e.g. shifting of resources and/or budget reallocations, horizontally or from higher to district levels. The evaluation will monitor such indirect changes, quantitatively through repeated PIPES measurements and qualitatively through in-depth interviews with DLH and SOT staff.

The PIPES questionnaire captures binary data on five aspects of surgical preparedness of the sample of facilities, namely procedures offered and the availability of personnel, infrastructure, equipment and supplies. Responses to individual categories will then be combined to compute an overall surgical capacity index score for each facility, which is comparable across hospitals and countries. The PIPES questionnaire will be administered directly by the research team to the DLH surgical staff (including representatives from surgery, anaesthesia and nursing). In order to improve reliability and internal validity [58] researchers will use a consensus approach to the completion of the questionnaire, where two to three key informants at each of the DLHs will be asked to discuss and validate the answers. The tool has been tested and validated [58]; however, so as to address gaps identified by other studies employing this instrument [59], we have added a short annex. This delves deeper into the obstacles and opportunities to surgical service provision flagged by the answers to PIPES, and it captures additional details on factors such as anaesthesia capacity, surgical staff expertise, referrals patterns, information management and quality control practices at facility level, based on lessons learned in the earlier COST-Africa project [17].

The PIPES questionnaire, and its annex, will be administered at regular intervals during the life of the project: at baseline (as part of the initial situation analysis), mid-term (month 12) and in the last year (month 24). The primary comparison to detect changes deriving from the intervention will be baseline versus endline data. For the parameters where no tool was available, we have developed tailored data collection instruments. Information on surgical procedures performed in the project sites as well as patients’ age, sex, condition requiring surgery, duration of hospital stay, immediate outcome and cadres of surgical staff involved, among others, will be gathered through a six-monthly review of DLH operating theatre (OT) registers. Relevant data will be organised into an electronic format to facilitate standardisation of records across hospitals. Staff skills’ levels will be tracked through a self-reported surgical confidence tool, covering surgery, anaesthesia and post-op care.

Comparable data from the PIPES questionnaire and OT registers will be cross-checked for further validation of responses and to minimise errors. The surgical confidence tool will be completed by the trainees themselves, anonymously, indicating only their profession. This will minimise the risk of possible bias in responses. Specialist supervisors will be responsible for distributing the forms during their quarterly visits to the districts and collecting them upon completion. As such, its target sample will only include intervention hospitals. All DL clinicians working with members of the SOT will be assessed.

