### Research sites

The intervention will be delivered in 30 district-level hospitals (DLHs) in three African countries—Malawi, Zambia and Tanzania—for 24 months. The evaluation will include 4 months of baseline data and 24 months of intervention data. Malawi, Zambia and Tanzania were chosen because of their political stability, long-term presence of the consortium members on the ground and logistical considerations related to feasibility of implementation. Malawi and Zambia were the settings of the previous COST-Africa project, whose findings led to the SURG-Africa intervention. In each country, a large catchment population was purposively selected in consultation with local ministries of health, the geographical focus is country-wide in Malawi; adjoining districts in Southern, Central, Western and Lusaka provinces in Zambia and the Northern Zone in Tanzania. Study sites (selected districts) will be determined by the location of referral institutions and respective DLHs that fall within the referral network of that referral hospital. A randomised design for the allocation of hospitals to the intervention and the control arms is not possible because of the small sample sizes (availability of suitable DLHs within these referral networks) and the nature of the intervention (described below). Control hospitals will therefore be located outside these areas and will refer patients to different referral hospitals. However, the risk of selection bias is low because DLHs are fairly homogeneous within each study country regardless of their location, thus reducing the chance of imbalance in characteristics in the distribution of treatment versus control groups [50–52]. Hospitals that do not meet the inclusion criteria (below) or that are already demonstrating significantly better surgical performance than would be expected at a DLH will be excluded from the sample. The precise selection of control hospitals will be determined by the results of the situation analysis conducted prior to the kick off of the intervention. The situation analysis will constitute the baseline for our study (month 0). It will collect information about the surgical capacity of district hospitals using theatre records (volume and range of surgery), Personnel, Infrastructure, Procedures and Supplies (PIPES) scores and additional questions about referral patterns, information management systems, quality control practices and availability of staff (NPCs) not covered by the PIPES questionnaire. This information will be analysed aiming to determine hospital suitability to be part of the intervention based on the following criteria.

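### With 4 baseline months against 24 intervention months, a register-based before-and-after count of 'new procedures', a component of the primary endpoint, would be biased upward

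*Protocol article*

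**What the plan says.** Objective 1 of the protocol article names the "number of common surgical procedures performed and types and numbers of new procedures introduced, which form the primary endpoint of the study". The Productivity row of Table 2 repeats the second component as "Types and numbers of new procedures introduced into DLHs". Both places plan two comparisons, before against after and intervention against control hospitals; the text adds that this is done for groups and for individual hospitals.

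Research sites fixes the observation periods: "The evaluation will include 4 months of baseline data and 24 months of intervention data". Data analysis describes the contrast as change from baseline to the end of the 24 intervention months.

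Two instruments serve the Productivity row: "PIPES questionnaire Monthly data collection from DLHs operating theatre registers". On the first, Objective 1 says "The PIPES questionnaire captures binary data on five aspects of surgical preparedness of the sample of facilities, namely procedures offered"; it is completed at months 0, 12 and 24 by consensus of two to three informants. On the two together: "Comparable data from the PIPES questionnaire and OT registers will be cross-checked for further validation of responses and to minimise errors".

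The article gives no look-back period, minimum count or equal-window rule for calling a procedure new, and does not say what happens when the questionnaire and the register disagree.

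**The concern.** Whether a procedure appears at all in a register depends on how long the register is read. A monthly volume can be rescaled for unequal periods; a first appearance cannot. With a follow-up window six times the baseline window, a procedure done once or twice a year is easily missed before and almost certain to be seen after. The count of new procedures starts at zero and can only rise.

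At stake is the before-and-after reading of a primary-endpoint component. It could show several new procedures per hospital where practice has not changed, and a single hospital's result has no control to offset this. Four months also cannot cover a full seasonal cycle.

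**Working it through.** The article states no expected number of new procedures and no procedure rates, so there is no figure of its own to reproduce. What follows is an illustration of size.

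**Inputs.** Baseline 4 months and follow-up 24 months (Research sites). Assumed: one established procedure in one hospital, occurring as a Poisson process at an unchanged rate of r cases per year. The rate is not in the documents, so a range is shown. The register alone decides, with all 24 months pooled.

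**Formulas.**
- Not seen at baseline: exp(−4r/12).
- Seen at least once in follow-up: 1 − exp(−24r/12).
- Falsely new: the product of these two.
- Reverse error (seen at baseline, never in follow-up): [1 − exp(−4r/12)] × exp(−24r/12).

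| r per year | Not seen in 4 months | Seen in 24 months | Falsely new | Reverse error |
|---|---|---|---|---|
| 0.5 | 0.846 | 0.632 | 0.535 | 0.057 |
| 1 | 0.717 | 0.865 | 0.620 | 0.038 |
| 2 | 0.513 | 0.982 | 0.504 | 0.009 |
| 3 | 0.368 | 0.998 | 0.367 | 0.002 |
| 4 | 0.264 | 1.000 | 0.264 | 0.000 |
| 6 | 0.135 | 1.000 | 0.135 | 0.000 |
| 12 | 0.018 | 1.000 | 0.018 | 0.000 |

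The maximum is 0.62, near one case a year. The reverse error never exceeds 0.06 in this range, so the net bias is upward. If a hospital had 10 such procedures (an assumed number), the expected false count would be 5.4, 6.2, 5.0 and 3.7 at 0.5, 1, 2 and 3 cases a year.

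**Between arms.**
- Same rates and windows: the expected difference is 0.
- Different rates, for example 2 a year in one arm and 4 in the other: 0.504 − 0.264 = 0.24 per procedure.
- Volume in the intervention arm rises by a factor f with no procedure added: the excess is exp(−4r/12) × [exp(−24r/12) − exp(−24rf/12)]. For f = 1.25 to 1.5 this is 0.069 to 0.123 at r = 0.5, 0.038 to 0.061 at r = 1, and 0.006 to 0.008 at r = 2.

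**Candidate rules under no change, at r = 0.5, 1, 2 and 3.**
- 4 against 24 months, with at least 3 follow-up cases: 0.07, 0.23, 0.39, 0.35. A minimum count alone is not enough.
- Equal 4-month windows: appearances have probability 0.13, 0.20, 0.25, 0.23. Disappearances have the same probability, so the expected net change in distinct procedures is 0.
- 12-month look-back plus at least 3 cases in 24 months, exp(−r) × P[Poisson(2r) ≥ 3]: 0.05, 0.12, 0.10, 0.05. At r = 1 this is 0.368 × 0.323 = 0.119. Excluding procedures reported at baseline PIPES would lower these further.

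**The case against.** A reader might infer that established procedures *will* be counted as new and that the primary endpoint is therefore positive by construction. The documents do not support that.

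- Nowhere is 'new' defined as absent from 4 register months and present in 24. The baseline-to-end-of-study wording leaves open whether the 24 months are pooled at all.
- Table 2 assigns PIPES as well as the registers. PIPES asks at month 0 which procedures are offered, with no stated 4-month limit, so a procedure done twice a year can be on record even if the register misses it. The cross-check is a real safeguard.
- Research objectives describes new procedures as introduced where the oversight team judges them appropriate, which visiting supervisors could observe directly in intervention hospitals.
- The index is to be built from core procedures found in the situation analysis. Rare procedures may not enter it, and for monthly procedures the error is only about 2%.
- Control hospitals share the artefact. Control hospitals are also meant to resemble intervention hospitals at baseline in productivity, PIPES scores and staffing.
- A full protocol or SAP may define 'new', and an article's silence on that is not itself a fault.

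All of this stands, and it limits the point to a conditional one. It does not remove it. The short baseline is a data-collection choice stated in the article, and a later definition cannot recover register history that was never extracted. The before-and-after and single-hospital comparisons are planned in their own right and get no protection from the controls. The cross-check has no rule for disagreement. Similarity on overall productivity does not ensure similar rates of infrequent procedures in purposively chosen arms.

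**Conclusion.** The point holds in conditional form. If 'new' is read from the registers over the stated windows, the before-and-after count is biased upward, with a false-new probability of about 0.26 to 0.62 per established procedure done 0.5 to 4 times a year, and little bias for procedures done monthly. This rests on a constant Poisson rate, on rates that the documents do not give, and on PIPES not being used to exclude established procedures.

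The between-arm comparison is much less affected: zero expected bias at equal rates, added noise, and some bias if rates of infrequent procedures differ between arms or if the intervention raises volume without adding procedures. The claim that the trial's overall primary result is positive by design goes beyond the documents.

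**What to change.** - Compare the number of distinct index procedures per hospital in windows of equal length covering the same calendar months before and after, by the same rule in both arms.
- Count a procedure as new only if it is not reported at baseline PIPES, is absent from the register look-back (extended to 12 months where registers allow), and is done at least a fixed number of times afterwards, for example 3. This also settles disagreement between sources: a procedure found in either one at baseline is not new.
- Base the conclusion on the between-arm difference. Report within-arm and single-hospital before-and-after counts of new procedures as descriptive only.

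The cost is a change of wording and some further extraction from registers the project already reviews. Fewer procedures will qualify as new. Older register data may be incomplete; the article itself says routine surgical data in most such countries are unreported or unreliable, so look-back completeness should be reported by hospital and arm. Without the longer look-back, matched 4-month windows leave most of the follow-up out of this comparison. Equal windows remove the bias under no effect, but they do not fully separate a new procedure from an existing one done more often; the PIPES and look-back exclusions reduce that overlap.

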## Research objectives

The specific objectives of this research study are as follows:To determine whether the intervention is able to affect change in surgical activity at district level. We will assess whether supervision and mentoring will enhance the capacity of district surgical teams, leading to changes in surgical activity. In particular, we expect to observe (1) an increase in the number of procedures regularly performed by the participating hospitals compared to surgical activity before the intervention, as more district clinicians will be trained in handling general surgical procedures and (2) a change in the range of surgical cases done in DLHs as new procedures will be introduced and performed by local teams, where the SOT deems this to be appropriate to local needs, staff skills and resourcesTo establish the feasibility of the intervention to improving skills of local surgical teams (including surgery, anaesthesia and nursing staff) as individuals and as a group. We will test whether the support offered through supervision and mentoring will change confidence (as a proxy measure of skills) and preparedness of local teams in performing essential surgical proceduresTo monitor whether the intervention can change referral practices, particularly whether it can reduce the number of unnecessary surgical cases referred by district hospitals compared to the number before the intervention because skills and confidence of DLHs clinicians are expected to improveTo determine the feasibility and acceptability of the remote consultation mechanism established by the intervention and to assess any changes in communication between DLHs and RHs and in clinical decision-making. The project’s mobile phone-based communication network will give DLH clinicians access to specialist opinion at RHs and will allow real-time consultations with RHs clinicians. The communication network will also facilitate timely feedback to district teams on referred cases

In parallel, the research will investigate process-related aspects of the intervention to determine feasibility and replicability of the proposed regular supervision model, particularly in light of the shortage of specialists at referral institutions and limited budgets. It will identify obstacles and enablers to DLHs supervision done by specialists located at RHs, to build an understanding of what processes need to be put in place for the supervision to be successful in achieving the above objectives.

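### Mortality is compared without regard to procedure mix, although the intervention is meant to change that mix in one arm only

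*Protocol article*

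**What the plan says.** In the protocol article, the productivity row of Table 2 (Objective 1) lists "Change in surgical mortality rates" as an indicator, measured by "Comparing differences: (1) before and after and (2) between intervention and control hospitals". The text below the table states that "the evaluation will track intra-hospital mortality rates to monitor possible changes in surgical outcomes as surgical activity is expected to increase". The Data analysis section plans frequency counts and comparisons of means from baseline to month 24, and mentions no stratification or standardisation.

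The Research objectives say what supervision should change: "an increase in the number of procedures regularly performed by the participating hospitals compared to surgical activity before the intervention"; "a change in the range of surgical cases done in DLHs as new procedures will be introduced and performed by local teams"; and, for referrals, "whether it can reduce the number of unnecessary surgical cases referred by district hospitals compared to the number before the intervention". The Study design section repeats the aim of avoiding unnecessary referrals. The Control hospitals section says that practice there continues as standard, without the project's supervision teams.

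The register review described under Objective 1 gathers the procedure performed, age and sex, together with "condition requiring surgery, duration of hospital stay, immediate outcome and cadres of surgical staff involved".

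**The concern.** A mortality rate over all operations is an average of procedure-specific risks weighted by how often each procedure is done. The intervention is designed to change those weights: more operations, new types of operation, and some patients kept who would have been sent on. Retained or newly accepted high-risk cases push the rate up. Added low-risk elective cases push it down and can hide harm elsewhere. The direction cannot be known beforehand.

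A control group removes changes that both arms share. This change is produced by the intervention in one arm, so it passes whole into the between-arm contrast, and the more the mix shifts, the larger the artefact can be.

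The stake is the safety reading. Mortality is the one patient-safety indicator in Tables 2 and 3, and the project intends its results to inform national scale-up of a model for safe district surgery. A false alarm or a false reassurance would both be costly.

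**Working it through.** The document gives no mortality rate, event count or case mix, so there is no figure of the plan to reproduce. The check asks whether the rate can move when procedure risks do not. All mixes and risks below are assumptions.

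**Formula.** Crude rate = Σ(n × r) / Σn over procedure groups, where n is the number of operations and r the risk of death.

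**Assumed baseline mix per 1,000 operations.** 700 caesareans, 200 low-risk elective, 100 high-risk.

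**Scenarios, each r held fixed.** A: 100 more high-risk cases. B: 300 more low-risk elective cases. C: 150 more low-risk and 50 more high-risk.

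Entries are expected deaths / operations = crude rate, with the ratio to baseline in brackets.

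| Assumed risks (caesarean / low / high) | Baseline | A | B | C |
|---|---|---|---|---|
| 0.2 / 0.2 / 3% | 4.8/1000 = 0.48% | 7.8/1100 = 0.71% (1.48) | 5.4/1300 = 0.42% (0.87) | 6.6/1200 = 0.55% (1.15) |
| 0.5 / 0.2 / 8% | 11.9/1000 = 1.19% | 19.9/1100 = 1.81% (1.52) | 12.5/1300 = 0.96% (0.81) | 16.2/1200 = 1.35% (1.13) |
| 1 / 0.5 / 15% | 23/1000 = 2.30% | 38/1100 = 3.45% (1.50) | 24.5/1300 = 1.88% (0.82) | 31.25/1200 = 2.60% (1.13) |

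Worked example, second row, scenario A: 700 × 0.005 + 200 × 0.002 + 200 × 0.08 = 3.5 + 0.4 + 16 = 19.9 deaths in 1,100 operations.

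**Control comparison.** If mix and risks in the control arm do not change, its before/after difference is zero and the difference-in-differences is the whole artefact: +0.229, +0.619 and +1.155 percentage points in A, and −0.065, −0.228 and −0.415 in B.

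**Masking.** Multiply every risk by 0.75, a true improvement, and scenario A still shows a rise: ratios 1.11, 1.14 and 1.13. Multiply every risk by 1.2, a true deterioration, and scenario B shows almost nothing: ratios 1.04, 0.97 and 0.98.

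**After standardisation.** With baseline shares w as fixed weights, the ratio is Σ(w × r after) / Σ(w × r before). With unchanged risks this is 1.00 in every scenario by construction. With all risks cut by 25% it is 0.75, and with all raised by 20% it is 1.20, so a true change is no longer hidden by the mix.

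**The case against.** The strongest reply is that the article never calls the rates pooled or unadjusted. It condenses a longer document, and how to stratify a secondary outcome is commonly left to an analysis plan that is not shown. Most of the fields needed are collected, so nothing prevents a stratified report. This lowers the weight of the point but does not answer it. The article does fix the comparison, as a change in rates before and after and between arms, and it makes the change in mix an aim of the intervention.

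Three further objections hold and limit the point.

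- **Role.** Mortality is monitored alongside the primary endpoint, which is procedure numbers and new procedures, in an exploratory pilot. No decision rule rests on it. A reader might infer that mortality is the project's only evidence on safety. That goes too far: the Study design section announces separate studies of the quality of a wider set of operations, and Objective 2 records immediate outcomes of referred patients at the referral hospitals.
- **Numerator.** The wording varies between surgical mortality, intra-hospital mortality and immediate outcome. A reader might infer that theatre registers miss deaths on the ward. The text does not show this. Duration of stay is gathered in the same review, which suggests that the record is followed to the end of the admission. What stands is that no single definition of death is given.
- **Remedy.** Standardising everything to the baseline mix would give newly introduced procedures zero weight, although harm there is one of the things to detect. They need separate reporting. Urgency is not among the listed fields, so standardising by it is not supported either.

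**Conclusion.** The concern holds as a point about a secondary monitoring outcome. As described, the mortality comparison can move in either direction through procedure mix alone, and the control arm does not correct it because the shift is an intended effect in the intervention arm.

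Only the size is uncertain. Under the assumed risks and mixes, the crude ratio ranges from 0.81 to 1.52 with procedure risks unchanged. These values show that the artefact can be large enough to matter. They do not forecast what these hospitals will see: the document supports no particular growth in high-risk surgery, and it says that new procedures will be introduced only where the supervision team finds them appropriate. The primary endpoint is not affected. An analysis plan that is not shown may already stratify, in which case the protocol needs only to say so.

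**What to change.** - Report the number of deaths and of operations, with 95% intervals, by arm and period for three groups: caesarean section, other index procedures done at baseline, and newly introduced procedures.
- For the before/after and between-arm contrast, restrict to procedures done at baseline and standardise to the baseline procedure mix, with the same weights in both arms and both periods. Add broad age bands only if numbers allow.
- Report newly introduced procedures separately and outside the standardised contrast, since they have no baseline weight.
- State one death definition, in-hospital death before discharge, and apply it identically in both arms and both periods.
- Label the contrast as descriptive.

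**Cost.** Mostly wording, because procedure, age and condition are already collected. Applying one death definition throughout may take some extra extraction effort. Deaths will probably be few, particularly in the 4 baseline months, so the intervals will be wide and should be shown as they are. Standardising by procedure does not remove a change in severity within a procedure, which is a further reason to keep the contrast descriptive.

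### The capacity row is labelled a controlled comparison, but both its indicators are defined on intervention staff only, and the confidence forms pass through the supervisors who give the training

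*Protocol article*

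**What the plan says.** The capacity row of Table 2 (Objective 1) has two indicators: "Number of intervention DLH staff who are reported as competent in doing index procedures" and "Intervention DLH staff self-reported surgical skills confidence levels". The instruments listed are the PIPES questionnaire and the self-reported confidence tool. One measurement entry covers both indicators: "Before-and-after controlled comparison".

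The text below the table describes a "before-and-after controlled comparison of the number of intervention DLH staff who is reported as competent in doing index procedures", and then introduces confidence as a further measure and a proxy for skills.

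Later in Objective 1 the handling of the confidence tool is set out. "The surgical confidence tool will be completed by the trainees themselves, anonymously, indicating only their profession". The article comments: "This will minimise the risk of possible bias in responses". Then: "Specialist supervisors will be responsible for distributing the forms during their quarterly visits to the districts and collecting them upon completion". And finally: "As such, its target sample will only include intervention hospitals".

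PIPES is handled differently. The research team administers it, two to three informants at each hospital agree the answers, and it is repeated at months 0, 12 and 24.

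**The concern.** A reader of Table 2 would expect the capacity result to be a difference in change between arms. The definitions do not supply one. For the confidence tool this is more than a matter of wording: control hospitals never receive the form, and no analysis plan can recover data that were not collected.

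The second specific aim under Research objectives is to test whether supervision changes confidence and preparedness. The Data analysis section deals with secular trends by assuming that they occur irrespective of allocation. That assumption helps only where the control arm is measured. Over 24 months, staff gain experience, some move (the Discussion expects this at intervention sites), and people asked repeatedly about their confidence may answer differently. If the result is reported as controlled, any of these could be credited to the supervision programme.

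The confidence tool has a second weakness. The people whose training is being judged hand out the forms and take them back. Leaving names off does not remove the incentive to give a courteous answer in that setting.

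**Working it through.** **No figure to reproduce.** The article gives no sample size, effect size or standard deviation for the capacity measures, so the main check is textual. The calculations only illustrate what follows.

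**Step 1: label against definition, by indicator.**

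| | Competence count | Self-reported confidence |
|---|---|---|
| Called controlled in Table 2 | yes (shared cell) | yes (shared cell) |
| Called controlled in the text | yes | no |
| Staff counted | intervention only | intervention only |
| Control hospitals explicitly left out | no | yes |
| Administered by | research team, if taken from PIPES | supervisors, at quarterly visits |
| Anonymous, profession only | not stated | yes |
| Instrument used in controls | yes, at least at baseline (Table 1; Control hospitals section) | no |

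Both columns lack a control series as written. In the left column the obstacle is the word intervention in the definition. In the right column it is the sampling itself.

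**Step 2: what a missing control can do (illustration).** Inputs from the article: 30 intervention hospitals; two-sided 5% significance. Assumed: a true effect of zero, a common drift of d standard deviations of hospital-level change, and a normal approximation. The probability that a before-after test rejects is

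Φ(d√30 − 1.96) + Φ(−d√30 − 1.96).

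- d = 0: 5.0%
- d = 0.10 (d√30 = 0.548): 8.5%
- d = 0.25 (d√30 = 1.369): 27.8%
- d = 0.50 (d√30 = 2.739): 78.2%

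With controls measured, drift shared by both arms cancels and the rate returns to 5%. The price is a larger standard error, by the factor √(1/30 + 1/n) / √(1/30). This is 1.41 for n = 30 controls and 1.73 for n = 15. The number of controls is assumed.

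**Step 3: loss of pairing (confidence tool only).** If the same people answer twice with within-person correlation r, the variance of the mean change is 2σ²(1 − r)/n when forms are linked. An unlinked analysis uses 2σ²/n. The ratio is 1/(1 − r), with r assumed:

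- r = 0.3: variance × 1.4, standard error × 1.20
- r = 0.5: variance × 2.0, standard error × 1.41
- r = 0.7: variance × 3.3, standard error × 1.83

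So unlinked intervals are too wide. Staff turnover shrinks this loss, because fewer people answer twice, but unlinked forms also cannot tell turnover from individual change.

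**Step 4: baseline.** The only stated route for the confidence form is the supervisory visit. On that procedure the earliest form is completed at the first visit, so the text fixes no measurement taken before the intervention begins.

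**The case against.** The strongest reply is that the conflict over confidence rests on one table cell shared by two indicators. The text applies the word controlled only to the competence count and says openly that the confidence tool is for intervention hospitals. That is fair, and it makes relabelling an adequate minimum repair. It does not make the table correct.

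A reader might go further and infer that the whole capacity assessment rests on unlinked anonymous forms handled by trainers. The article does not support this. Those features belong to the confidence tool alone. The competence count can be taken from PIPES, which the research team administers and which is already used in control hospitals at least at baseline, and the two groups are to be followed and compared.

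A reader might also infer that confidence scores are biased upward. Courtesy and growing experience make that plausible, but newcomers replacing trained staff, or staff judging themselves more strictly, would lower scores. Only a risk of bias is shown. Nor does loss of pairing make the test too liberal: with positive correlation it makes the test conservative, and hospital-level change can still be compared if forms are kept by hospital. That profession alone may identify someone in a small team is reasonable, but the article gives no team sizes.

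Finally, the specific aim on confidence does not stand on this form alone: repeated PIPES scores, the competence count and the qualitative interviews also bear on it. The study is an exploratory pilot with surgical productivity as its primary endpoint. This limits the severity and leaves the contradiction in place.

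**Conclusion.** The capacity row is wrong as written. It claims a control that neither indicator's definition provides, and for confidence the control data will not exist. This follows from the text alone. A change in confidence can be described, but not attributed to the intervention.

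The claim that anonymity minimises bias is not secured while supervisors collect the forms. The size and direction of any resulting bias are unknown. The rejection rates of 8.5% to 78.2% depend entirely on assumed drift of 0.10 to 0.50 SD and show only that modest drift would matter. The loss of pairing is a secondary cost in precision.

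Should-fix: the primary productivity comparison is unaffected.

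**What to change.** 1. Define the competence count in intervention and control hospitals alike, taken from the research-team PIPES and its annex at months 0, 12 and 24, and compare change between arms. The cost is wording, plus any control-hospital PIPES follow-up not already intended.
2. For confidence, remove the word controlled from Table 2 and report an uncontrolled before-after change, not attributed to the intervention. This costs nothing. The alternative is to give the form in control hospitals at the PIPES visits. That is a real burden: PIPES needs two to three informants per hospital, whereas the confidence tool is meant for every clinician working with the supervisors, so whole control teams would have to be surveyed.
3. Have confidence forms returned sealed to the research team and not to the supervisors, with a baseline completed before the first supervisory visit. The cost is envelopes and one earlier distribution. Soften the statement on bias to match.
4. Optional: a self-generated code to link a respondent's forms. It recovers the precision in step 3 of the working but weakens perceived anonymity, so it is a judgement for the team.

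Item 3 and any control collection must be settled before visits start, because a missed baseline cannot be recovered.
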